##### **Treatment visits (C4+, D113+)**

The treatment visits starting from the 4th treatment cycle should be carried out according to the following procedures:

- Drug dispensing (drug for 2 treatment cycles), comprehensive physical examination, body weight measurement, ECOG PS scoring, vital signs measurement, laboratory tests (clinical biochemistry, hematology, and urinalysis), and 12-lead ECG will be performed once every 8 weeks
- Ophthalmological examinations will be performed as clinically indicated throughout the treatment period, and the examination items will be determined by the investigator based on the subject's condition
- Echocardiography will be performed when clinically indicated
- Response evaluation in solid tumors will be performed as per RECIST 1.1 once every 8 weeks
- AEs and concomitant medications will be recorded

#### **9.1.3 Follow-up period**

##### **9.1.3.1 EOT follow-up**

The end-of-treatment (EOT) follow-up refers to the visit procedures to be completed when a subject completely discontinues the study treatment, which is required to be completed within 7 days after the last dose. The procedures include the following:

- Comprehensive physical examination, body weight measurement, ECOG PS scoring, vital signs measurement, laboratory tests (clinical biochemistry, hematology, and urinalysis), 12-lead ECG, echocardiography, and ophthalmological examination (when clinically indicated)
- Response evaluation in solid tumors as per RECIST 1.1
- AEs and concomitant medications will be recorded

At the EOT visit, if there are safety examination results (comprehensive physical examination, body weight measurement, ECOG PS scoring, vital signs measurement, laboratory tests, and 12-lead ECG examination) within 7 days before the visit, repeated examination will not be required; if there are RECIST response evaluation results and echocardiography results within 4 weeks before the visit, repeated evaluation/measurement will not be required.

##### **9.1.3.2 Safety follow-up (28-day follow-up)**

Safety follow-up refers to visit procedures to be completed during the 28 days after treatment discontinuation (discontinuation of investigational medicinal product administration) to follow up on the ongoing and new AEs. AEs, for which outcomes are not available, should be followed up until outcomes are available or AEs are stable, which is not subject to the 28-day follow-up period. Only investigational medicinal product/procedure-related SAEs will be collected thereafter. The procedures include the following:

- Documentation of AEs (new AEs or follow-up information of AEs ongoing at treatment discontinuation)
- Documentation of concomitant medications (all concomitant medications including anti-tumor treatment)

### 9.1.3.3 Progression follow-up

Progression follow-up refers to the visit procedures to be completed for subjects who discontinue treatment for reasons other than progressive disease. The subjects will undergo assessment per RECIST 1.1 once every 8 weeks (relative to the date of enrollment). The procedures include the following:

- Response evaluation in solid tumors once every 8 weeks until progressive disease assessed by investigator per RECIST 1.1 (all systemic, intracranial, and extracranial)
- Documentation of concomitant medications: Only details of subsequent anti-tumor treatments will be documented until progressive disease (all systemic, intracranial, and extracranial)
- Subjects who experience progressive disease before completing the 28-day safety follow-up should continue undergoing the safety follow-up until 28 days after treatment discontinuation

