| 

Screening period	Treatment period	Follow-up period	

Age ≥18 years old

Histologically or cytologically diagnosed with NSCLC

Metastases to brain parenchyma confirmed by imaging

Genetically confirmed as EGFR-sensitive mutations

Have not received any systemic treatment after diagnosis

ECOG PS 0–1

	

Aumolertinib, 165 mg, p.o., QD

	

Response evaluated per RECIST 1.1 once every 8 weeks until progressive disease
Primary study endpoint:
12-month PFS rate
Secondary study endpoints:
iPFS, iORR, iDCR, iDoR
ORR, DoR, DCR, OS
Safety

Patients who have discontinued treatment are followed up once every 8 weeks for progressive disease status until progressive disease, and once every 12 weeks after progressive disease for survival

	

 |                                                                 |                                                                                                                             |                                                                                                                                                                                                                                                                                                                                                                                                                                                                  | Screening period | Treatment period |  | Follow-up period | 

Age ≥18 years old

Histologically or cytologically diagnosed with NSCLC

Metastases to brain parenchyma confirmed by imaging

Genetically confirmed as EGFR-sensitive mutations

Have not received any systemic treatment after diagnosis

ECOG PS 0–1

 | 

Aumolertinib, 165 mg, p.o., QD

 |  | 

Response evaluated per RECIST 1.1 once every 8 weeks until progressive disease
Primary study endpoint:
12-month PFS rate
Secondary study endpoints:
iPFS, iORR, iDCR, iDoR
ORR, DoR, DCR, OS
Safety

Patients who have discontinued treatment are followed up once every 8 weeks for progressive disease status until progressive disease, and once every 12 weeks after progressive disease for survival

 |

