**Figure 1. Schematic overview of the study**

• **Screening period (D–28 to D–1)**

Inpatients or outpatients will be screened after signing the informed consent form and undergo relevant laboratory tests and assessments. Subjects who meet all the inclusion criteria and do not meet any of the exclusion criteria may be enrolled.

• **Treatment period (C1+, D1+)**

High-dose aumolertinib group: Oral administration of 165 mg aumolertinib tablets once daily (55 mg/tablet, 3 tablets/day).

Each treatment cycle consists of 28 days of continuous administration. After treatment is started, efficacy will be evaluated once every 8 weeks as per RECIST 1.1. Patients will continue treatment until progressive disease assessed by investigator per RECIST 1.1 or until the withdrawal or discontinuation criteria are met. Patients may continue to receive the treatment even if progressive disease per RECIST 1.1 occurs as long as they still benefit from the treatment as judged by investigator (see Section 12.1.3 or 9.1.3.4 for details); if it is decided to continue the treatment, the baseline and follow-up plan will not be affected by the additional courses of treatment. Once the treatment is discontinued due to lack of clinical benefit upon judgment, it cannot be started again.

• **Follow-up period**

Subjects who discontinue the treatment due to meeting the discontinuation criteria should complete the treatment discontinuation follow-up, the 28-day safety follow-up after treatment discontinuation, and survival follow-up once every 12 weeks as specified in the study plan.

Subjects without progressive disease at treatment discontinuation will be followed up once every 8 weeks until progressive disease assessed by investigator per RECIST 1.1 (intracranial, extracranial, and systemic), even if the subject has received other anti-tumor treatments; after progressive disease, the subjects will be followed up for survival once every 12 weeks as specified in the study plan.

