### **7.8 Treatment Discontinuation and Withdrawal from Study**

#### **7.8.1 Treatment discontinuation**

Treatment discontinuation means that the subject no longer receives the study treatment due to the following reasons after the start of study treatment, but is not withdrawn from the study and will complete subsequent follow-ups as scheduled.

1. Progressive disease (refer to 2 in case of free medication)
2. Disease progression after free medication
3. Adverse event
4. Poor compliance

5. Major protocol violation
  6. Patients are no longer eligible to continue with the study treatment as believed by the investigator or funder (e.g., psychiatric disorders or social status that may interfere with subject's rights, safety, cooperation, and participation in this study)
  7. Patients request for treatment discontinuation but agree to continue to be followed up
  8. Patients withdraw the informed consent
  9. Loss to follow-up
  10. Pregnancy
  11. Study termination or site closure
  12. Patients who develop corneal ulcer or interstitial pneumonia should permanently discontinue the treatment
- Every effort should be made to obtain information of patients who discontinue study treatment, including information concerning EOT follow-up and the safety follow-up thereafter. The primary reasons for study treatment discontinuation should be documented on the corresponding eCRF. A patient's request for withdrawal from the study at the same time must be documented in the source documents, with the investigator's signature affixed. In addition, patients who discontinue study treatment due to reasons other than PD should undergo tumor assessments as scheduled until documented PD, unless the patient withdraws from the study due to any of the reasons described in 7.8.2.

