**Table 3. Determination of disease progression, subsequent anti-tumor therapies, and data collection**

| Systematic review | Intracranial lesions | Extracranial lesions | Subsequent treatment                                                   | Subsequent anti-tumor evaluation                                                                               |
|-------------------|----------------------|----------------------|------------------------------------------------------------------------|----------------------------------------------------------------------------------------------------------------|
| PD                | PD                   | PD                   | Treatment discontinuation                                              | Continue evaluation until progressive disease as per RECIST 1.1 (all intracranial, extracranial, and systemic) |
| PD                | PD                   | Non-PD               | Treatment discontinuation                                              |                                                                                                                |
|                   |                      |                      | Continue aumolertinib + brain local treatment                          |                                                                                                                |
| PD                | Non-PD               | PD                   | Treatment discontinuation                                              |                                                                                                                |
|                   |                      |                      | Continue aumolertinib + extracranial local treatment (oligometastasis) |                                                                                                                |
| Non-PD            | PD                   | PD                   | Treatment discontinuation                                              |                                                                                                                |
| Non-PD            | PD                   | Non-PD               | Treatment discontinuation                                              |                                                                                                                |

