#### **12.1.4 Duration of response (DoR)**

DoR is defined as the time from the date of first compliance with response to the date of PD or death due to any cause. The end date of the response should be consistent with the date of the endpoint PFS. The start of DoR is defined as the latest date of the visit at which PR or CR criteria are first met. If a patient does not progress after a response, the censored time for PFS will be used for DoR.

Intracranial duration of response (iDoR) and systemic duration of response (DoR) will be assessed separately.

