## **4. Tumor Response Evaluation**

### **4.1 Evaluation plan**

CT examinations of the chest and abdomen (including the liver and adrenal glands) will be used to assess tumor burden at baseline and follow-up. CT with intravenous (IV) contrast is the preferred method. MRI should be used when CT is not feasible or medically contraindicated.

Baseline tumor assessment, which should be performed  $\leq 28$  days prior to start of study treatment, should involve all

regions in which diseases under assessment are known to metastasize, and potentially involved regions should be additionally assessed based on signs and symptoms of individual patients. Follow-up assessments should be performed every 6 weeks ( $\pm 7$  days) after the start of treatment until discontinuation of study treatment or withdrawal of informed consent. Imaging examination should also be performed at follow-up if new lesions are suspected at other sites.

If unscheduled assessments are performed and the patient has no progression, every effort should be made to enable the patient to perform subsequent assessments at the scheduled visits. This schedule will be followed in order to minimize any unintentional deviations due to the assessment of some patients at a follow-up frequency different from that for other patients.

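### Imaging stop rules conflict with Table 3, so brain scans could end before intracranial progression, and iDoR has no end date of its own

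*Protocol*

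**What the plan says.** The protocol makes three assessments at progression (systemic, intracranial, extracranial) and names iPFS and iDoR as secondary endpoints. Section 12.1.2 counts only intracranial PD or death as an iPFS event.

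The rules on how long imaging runs are spread over several places:

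- **Section 9.1.3.4, Table 3**, for patients after any progression: "Continue evaluation until progressive disease as per RECIST 1.1 (all intracranial, extracranial, and systemic".
- **Section 9.1.3.3**, for "subjects who discontinue treatment for reasons other than progressive disease": 8-weekly evaluation "until progressive disease assessed by investigator per RECIST 1.1 (all systemic, intracranial, and extracranial".
- **Section 6.1**, follow-up period: patients without PD when treatment stops are imaged until PD, with all three assessments named; then "after progressive disease, the subjects will be followed up for survival once every 12 weeks as specified in the study plan".
- **Synopsis**: patients off treatment are "followed up once every 8 weeks for progressive disease status until progressive disease", and after that contacted for survival.
- **Section 7.8.1**: "patients who discontinue study treatment due to reasons other than PD should undergo tumor assessments as scheduled until documented PD".
- **Appendix B, tumor assessment footnote**: every 8 weeks until PD is confirmed under RECIST 1.1, including after treatment stops; no compartment is named.
- **Appendix D 4.1**: assessments run "until discontinuation of study treatment or withdrawal of informed consent".

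On duration of response, section 12.1.4 says: "The end date of the response should be consistent with the date of the endpoint PFS". It applies the PFS censoring time to responders who have not progressed. It then says that iDoR and systemic DoR are assessed separately, and gives iDoR no end or censoring date of its own.

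**The concern.** Extracranial PD is not an iPFS event. A patient whose disease grows outside the brain while the brain is controlled remains at risk for iPFS and needs further brain scans. Table 3 provides them. A site working from Appendix D, or reading an unqualified PD as the first PD, could stop them.

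Two things would follow. iPFS would be censored at about the time of extracranial PD or treatment stop, and later intracranial progressions would not be seen. If extracranial and intracranial progression tend to go together, that censoring is informative and flatters intracranial control; if they are independent, the loss is of events and precision. Separately, an iDoR closed on the systemic PFS date would be too short for responders who first progress outside the brain.

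The imaging part cannot be left to the SAP, because scans that were never taken cannot be recovered at analysis. About 20 sites are planned, so uneven practice is foreseeable.

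**Working it through.** The protocol gives no figure on this point, so the check is mainly a comparison of texts.

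**Step 1. Trace one patient.** The patient stops treatment because of extracranial PD, the brain still being controlled. Are brain scans continued?

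| Text | Whom it addresses | Imaging ends at | This patient |
|---|---|---|---|
| 9.1.3.4, Table 3 | after any progression | PD in all three assessments | scans continue |
| 9.1.3.3 | stopped without PD | PD in all three assessments | not addressed |
| 6.1, follow-up period | stopped without PD | PD, all three assessments named | not addressed |
| 7.8.1 | stopped without PD | documented PD, compartment not named | not addressed |
| Synopsis | all who stop | PD, compartment not named | could stop |
| Appendix B footnote | all treated | PD, compartment not named | could stop |
| Appendix D 4.1 | all treated | treatment discontinuation | stops |

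Appendix D 4.1 contradicts Table 3 outright. The synopsis, 7.8.1 and the Appendix B footnote contradict it if PD means the first PD, and they do not say otherwise. Sections 6.1 and 9.1.3.3 use a stop compatible with Table 3 but leave out the patient who stops because of PD. Section 6.1 cites 9.1.3.4 only for treatment continued beyond PD; 9.1.3.3 does not cite it.

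**Step 2. Is Table 3 clearly the governing text?** Not clearly. Section 9.1.3.4 introduces it as recommendations, while section 9.1 sends sites to Appendix B for the overall schedule. Section 9.1.3.5 records response and progression data every 12 weeks during survival follow-up but requires no RECIST imaging, so it offsets the loss only in part.

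**Step 3. iDoR.** Section 12.1.4 refers to PFS without qualification. Section 12.1.2 defines both systemic PFS and iPFS. If PFS is taken as systemic, a patient with an intracranial response and later extracranial PD has iDoR ended at the extracranial PD, although the intracranial response persists.

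**Step 4. Illustration of direction.** Take the protocol's alternative of 60% PFS at 12 months. Assume constant hazards, independent intracranial and extracranial progression, no deaths, systemic PD at whichever comes first, and no treatment or imaging beyond first PD. The share f of first progressions that are extracranial is not in the protocol; 30%, 50% and 70% are assumed.

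- Total hazard: λ = −ln(0.60)/12 = 0.0426 per month.
- Intracranial hazard: λᵢ = λ(1 − f).
- Intracranial events by month T with full imaging: 1 − exp(−λᵢT). Events seen if imaging stops at first PD: (1 − f)(1 − exp(−λT)).
- Share unseen = 1 − seen/full. Worked for f = 50%, T = 20: full = 1 − exp(−0.4257) = 0.3467; seen = 0.5 × (1 − exp(−0.8514)) = 0.2866; unseen = 1 − 0.2866/0.3467 = 17%.
- Median time from treatment start to intracranial progression: ln 2/λᵢ. If it is ended on the systemic date instead: ln 2/λ = 16.3 months.

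| Assumed f | Unseen by 20 months | Unseen by 26 months (6 enrollment + 20 follow-up) | Median, intracranial clock | Median, ended on systemic date |
|---|---|---|---|---|
| 30% | 11% | 13% | 23.3 | 16.3 |
| 50% | 17% | 21% | 32.6 | 16.3 |
| 70% | 24% | 29% | 54.3 | 16.3 |

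These medians run from treatment start, not from response, so they show the direction of the iDoR error and not its size.

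**The case against.** The best defense is that the sections divide the work. Section 9.1.3.3 handles patients who stop without PD, and the next section, 9.1.3.4, handles patients after any progression; the patient traced above belongs there. Section 10.2.1 also cites 9.1.3.4 beside its own stop rule. Sections 6.1 and 9.1.3.3 name all three assessments, and 7.8.1 does not say that patients who stop for PD get no imaging.

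This stands in large part. A reader might infer that 6.1 and 9.1.3.3 end imaging at first progression, or that most of the protocol opposes Table 3. The documents do not support that. The words on survival follow-up in 6.1 come after a stop that names all three assessments and concern patients who stopped without PD; silence on the others is not a prohibition. What these sections lack is a pointer. The defense does not reach Appendix D 4.1, or the unqualified PD in the synopsis, 7.8.1 and the Appendix B footnote.

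On iPFS censoring, 12.1.2 censors at the last RECIST assessment and carries the same principles to iPFS, so that rule is largely in place. On iDoR, the promise of separate assessment makes pairing with iPFS a natural reading. The text does not state it, though, and the literal reading gives a different date.

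**Conclusion.** The point holds as an inconsistency of moderate weight that should be corrected. Sites following Table 3 preserve iPFS, so the intracranial endpoints could be cut short; it is not established that they would be.

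The conflict between Table 3 and a stop at first PD does not affect the primary endpoint, taking PD as the systemic call, because systemic PFS is settled at that date. Appendix D 4.1 reaches further if taken literally: it would also end imaging for a patient who stops treatment before any PD, against 12.1.2.

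The number of patients affected cannot be derived from the protocol. A reader might reason that 63 × 0.40 = 25.2 patients have a PFS event by month 12 and that, with 30% to 70% of these progressing only outside the brain, 8 to 18 patients are affected (25.2 × 0.3 = 7.6; 25.2 × 0.7 = 17.6). The documents do not support this as an estimate. The share is assumed, some of the events are deaths, Table 3 lets some patients continue treatment after extracranial PD, and iDoR concerns intracranial responders only. The percentages in the working rest on the same assumed shares. Informative censoring of iPFS is likewise a possibility; under independence only events and precision are lost.

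**What to change.** 1. Reconcile Appendix D 4.1, the Appendix B tumor assessment footnote, the synopsis and 7.8.1 with Table 3, so that imaging for the intracranial endpoints continues until intracranial PD whatever the extracranial status.
2. In the follow-up text of 6.1 and in 9.1.3.3, add a cross-reference to 9.1.3.4 for patients who stop treatment because of PD.
3. In 12.1.4, state that iDoR ends or is censored on the iPFS date, and DoR on the systemic PFS date.

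The cost is an amendment to wording and a notice to sites. No scans are added beyond those Table 3 already requires, and the treatment options in Table 3 are untouched. The change should be made while patients are still being imaged.

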### 9.1.3.4 Follow-up of patients after any disease progression

At the time of disease progression assessment, 3 sets of assessments will be performed in this study: systematic assessment, intracranial assessment, and extracranial assessment. During the overall assessment, extracranial and intracranial target lesions (no more than 5 target lesions in the whole body and at least one target lesion in the skull) will be selected according to RECIST 1.1, and then the selected intracranial and extracranial lesions will be subjected to separate intracranial and extracranial response evaluation according to the RECIST 1.1. There is no need to select additional intracranial or extracranial target lesions. See Table 3 for systemic, intracranial, and extracranial disease progression, subsequent anti-tumor therapies, and recommendations for data collection.

